### Statistical analysis

Sample size was determined prospectively as described in a previous study that used similar outcome measurements [21]. The following formula was used to estimate sample size [26]:

A previous study reported [21] an improvement of 18.0 in the main outcome NDI index score after treatment with 50 mg itopride. In this study, we anticipate an improvement of no less than 15.0 after acupuncture treatment; however, there are no previous data regarding NDI scores for the treatment of FD using acupuncture. Accordingly, an improvement of 3.0 in the NDI scores of two groups will be considered minimally significant. Standard deviation was defined as 22.0, according to the previous study [21]. Calculations were performed using 90% power and a 5% significance level, resulting in an estimated 120 patients per group. Thus, we must enroll 720 patients in the six groups, to allow for a 15% withdrawal rate.

The two-sided null hypotheses to be tested include:

(1) The primary outcomes of the acupoint treatment groups will be equivalent to those of the itopride control group.

(2) The primary outcomes of the acupoint treatment groups will be equivalent to those of the non-acupoint control group.

(3) The primary outcomes of the acupoint treatment groups will be equivalent to each other.

We will test these hypotheses with a significance level of P < 0.05. The first step of the analysis will involve comparing the baseline characteristics of the groups. The second step will be to compare the efficacy of acupoint and itopride in the treatment of FD. The third step will involve comparing the acupoint treatment group with the non-acupoint control group. If acupoint treatment is more effective than non-acupoint treatment in the treatment of FD, the fourth step will involve comparing the efficacy of four acupoint treatments.

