We choose itopride as the drug control because it has been shown to be an effective drug for FD. Furthermore, itopride caused fewer adverse events than did other gastrointestinal prokinetic agents [21]. Therefore, we will attempt to maintain a non-inferiority design because acupuncture is associated with no significant side effects. However, our trial will be limited by our inability to blind patients from knowing whether they are receiving acupuncture or itopride treatment. This factor may cause a high drop-out rate in the itopride group because patients will expect to receive acupuncture treatment when they join the trial. To prevent the expected high drop-out rate, patients in the itopride group will be provided with 10 sessions of free acupuncture after the entire trial has been completed.

Central randomization, a strict and complete form of randomization, will be used in this trial. This method not only provides rapid determination of group assignment, but also ensures adequate allocation concealment. In this trial, we will use transcutaneous electric acupoint stimulation (HANS) to avoid the performance bias generated by acupuncture practitioners. This method will provide accurate electric stimulation to ensure that every patient receives the same level of treatment.

We have devoted much effort to defining the non-acupoint control groups because the locations of non-acupoint treatments will differ from those described in the literature. Most Chinese studies have selected non-acupoints that lie beside the therapeutic acupoint, and halfway between the two lines or two acupoints [24]. However, reports in the Western literature have recorded the location of non-acupoints differently [29,30]. In our previous trial, we designed our two control groups according to the consensus of a panel of acupuncture experts. Thus, the non-acupoint control group in the current study was defined according to the first phase of our ***973 program***.

Briefly, this trial aims to determine if acupuncture is an effective treatment for FD. We will also assess differences in the specific effects of acupoints, as described in traditional theories. Certain procedures described herein, such as the randomization procedure, as controlled by central randomization system, and the standardized protocol for acupuncture manipulation, can be applied to future acupuncture studies.

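### The itopride comparison is described as attempted non-inferiority, but the printed hypothesis is a two-sided test of no difference, which cannot support a non-inferiority conclusion

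*Protocol article*

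**What the plan says.** Two places in the protocol article describe the comparison with itopride.

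- **Methods, Statistical analysis.** The list of hypotheses opens with "The two-sided null hypotheses to be tested include". The first is "The primary outcomes of the acupoint treatment groups will be equivalent to those of the itopride control group". The decision rule is "We will test these hypotheses with a significance level of P < 0.05".
- **Discussion**, in the paragraph on the choice of drug control: "we will attempt to maintain a non-inferiority design because acupuncture is associated with no significant side effects".

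The planning figures are also in Statistical analysis. The itopride effect is "an improvement of 18.0 in the main outcome NDI index score after treatment with 50 mg itopride", and for acupuncture "we anticipate an improvement of no less than 15.0 after acupuncture treatment". From these the article takes 3.0 points: "an improvement of 3.0 in the NDI scores of two groups will be considered minimally significant". The SD is 22.0. The result is "Calculations were performed using 90% power and a 5% significance level, resulting in an estimated 120 patients per group", said to allow for 15% withdrawal.

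The article calls no figure a non-inferiority margin. It gives no one-sided alternative and no confidence-interval rule for this comparison.

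**The concern.** A non-inferiority comparison takes as its null that the new treatment is worse than the control by at least a margin, and tries to reject it. Hypothesis 1 takes as its null that there is no difference. Rejecting it shows a difference; not rejecting it leaves the question open. The two passages therefore describe different tests, and an analysis plan that added a margin later would have to replace hypothesis 1, not supplement it.

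The comparison with itopride is the second step of the planned analysis and part of how the trial will judge whether acupuncture works. If the label and the test stay as they are, a non-significant P value could later be presented as showing that acupuncture is no worse than the drug. Low precision makes a non-significant result more likely, so imprecision would favour that reading.

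**Working it through.** **Inputs** (all from the protocol article): SD 22.0; 120 per group; 15% withdrawal, so 120 × 0.85 = 102; itopride improvement 18.0; acupuncture improvement at least 15.0; two-sided 5% level; 90% power. The figures below are for a plain comparison of two means with a normal approximation.

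**1. The plan's own figure.** For a difference of 3.0 at two-sided 5% and 90% power, n = 2 × (1.960 + 1.282)² × 22² / 3² gives 1,131 per group. One-sided 5% gives 922. The stated 120 is not reproduced. The formula itself is missing from the text available to me. This is a separate matter, and it enters here only because 120 fixes the precision.

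**2. Standard errors**, SE = 22 × √(1/n₁ + 1/n₂).

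| Comparison | n₁ v n₂ | SE | 95% CI half-width |
|---|---|---|---|
| One arm v itopride | 120 v 120 | 2.84 | 5.6 |
| One arm v itopride | 102 v 102 | 3.08 | 6.0 |
| Four arms pooled v itopride | 480 v 120 | 2.25 | 4.4 |
| Four arms pooled v itopride | 408 v 102 | 2.44 | 4.8 |

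Both versions are shown because hypothesis 1 does not say whether the acupoint arms are pooled.

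**3. Chance of a non-significant result when acupuncture is truly worse by d**, 1 − Φ(d/SE − 1.96), the other tail being negligible or included.

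| True deficit | One arm, 120 | One arm, 102 | Pooled, 480 v 120 | Pooled, 408 v 102 |
|---|---|---|---|---|
| 3 points | 82% | 84% | 73% | 77% |
| 6 points | 44% | 50% | 24% | 31% |

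Example: 6/2.84 − 1.96 = 0.15, and 1 − Φ(0.15) = 44%. A deficit of 6 points is one third of the 18.0 assumed for itopride. It is chosen for illustration.

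**4. A non-inferiority test, if 3.0 were the margin.** This is an assumption, because the article does not give 3.0 that role. Power = Φ((3.0 − true deficit)/SE − 1.96).

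- True equality, one arm: Φ(3/2.84 − 1.96) = 18% with 120, and Φ(3/3.08 − 1.96) = 16% with 102. Pooled, the corresponding figures are 27% and 23%.
- True deficit 18.0 − 15.0 = 3.0, the largest that the article anticipates: Φ(−1.96) = 2.5% at any sample size.
- Acupuncture 3 points better, which the wording allows: Φ(6/2.84 − 1.96) = 56% with 120, and Φ(6/3.08 − 1.96) = about 50% with 102, one arm.

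**5. Margin that the planned size can exclude** with 90% power at true equality, (1.960 + 1.282) × SE: 9.2 points (120) or 10.0 points (102) for one arm; 7.3 or 7.9 pooled. For one arm that is 9.2/18.0 = 51% to 10.0/18.0 = 56% of the assumed itopride improvement.

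**The case against.** The non-inferiority remark is a single hedged sentence in the Discussion. Neither the abstract nor the Methods uses the term, so a reader may take the two-sided hypotheses as operative and the Discussion sentence as loose wording. That is a fair reading. It makes dropping the wording a sufficient repair, but it does not reconcile the two passages as they stand.

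Three stronger inferences are tempting and should be resisted.

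- **That a non-significant result would pass as success.** No section says so. The second analysis step says only that efficacy will be compared. The risk comes from combining the label with this null; it is not a rule in the plan.
- **That the anticipated effect sits exactly on the margin, so a proper non-inferiority test could not succeed.** The 15.0 is a floor, so 3.0 is the largest anticipated deficit, not the expected one. The 3.0 is never called a margin and could equally be a smallest difference of interest. The 2.5% holds only for that worst case and that assumed margin.
- **That the per-arm figures are the only ones.** Hypothesis 1 can be read as pooling the arms, and the article's third analysis step refers to a single acupoint group. Pooling gives the smaller figures shown above. The planned repeated-measures and site-adjusted mixed models may also improve precision, by an amount that the article gives no basis for computing.

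A margin may also be given in a full protocol or analysis plan that is not shown, so its absence here is not the point. A per-protocol analysis is likewise commonly left to that plan. What stands is that the printed hypothesis contradicts the printed design label, and neither greater precision nor pooling turns a test of no difference into a non-inferiority test.

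**Conclusion.** The contradiction is real: hypothesis 1, as printed, cannot establish non-inferiority unless acupuncture is shown to be superior. The article does not commit itself to reading P > 0.05 favourably, but such a result would carry little weight. A true 6-point deficit would be missed in about 44% to 50% of trials per arm, or 24% to 31% pooled. If 3.0 were adopted as the margin, non-inferiority power per arm would be about 16% to 18% at true equality and 2.5% at the worst-case anticipated deficit.

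These sizes assume SD 22.0, 120 to 102 patients per group and an unadjusted comparison of means. The contradiction itself depends on none of them.

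**What to change.** Reconcile the two passages before unblinding, in one of two ways.

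- **(a) Keep non-inferiority.** Replace hypothesis 1 with H0: itopride minus acupuncture mean NDI improvement is at or above a stated and justified margin. Claim non-inferiority only if the upper bound of the two-sided 95% confidence interval, in NDI points, lies below that margin. Say whether the four acupoint arms are pooled or tested separately. State that, with 90% power at true equality, the planned size excludes only a margin of about 9 to 10 points per arm, or about 7 to 8 pooled.
- **(b) Drop non-inferiority.** Remove the wording from the Discussion, report the estimated difference with its 95% confidence interval, and state that P > 0.05 will not be reported as equivalence or non-inferiority.

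If no margin of the size in (a) can be defended, (b) is the workable choice at the planned size. Either way the cost is a change of wording and a less favourable claim about acupuncture against itopride. Treatment, recruitment and data collection are unaffected.

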### Rationale for selecting acupoints

The acupuncture treatment protocol is consistent with the principles of traditional acupuncture theories. These principles state that FD is in close proximity to the stomach meridian; hence, it is reasonable that the acupoint corresponding to the stomach meridian would be most effective at treating this condition. We also chose to study the gallbladder meridian because it is anatomically close to the stomach meridian and therefore may achieve similar effects. Furthermore, traditional acupuncture theories maintain that specific points convey specific therapeutic effects. Thus, the specific acupoint corresponding to the stomach meridian would be expected to be more effective than a non-specific acupoint of the same meridian. Therefore, we selected the most frequently used specific and non-specific acupoints of the stomach meridian, according to the results of a previous review of ancient and modern literature. According to traditional acupuncture theories, the alarm and transport points are considered specific points. Alarm points (Front-Mu points) are specific points on the chest or abdomen where the qi of the respective viscera are concentrated, whereas transport points (Back-Shu points) are specific points on the back where the qi of the visceral organs are infused. Both alarm points and transport points can be used to treat diseases of specific Zang-Fu organs; for example, Zhongwan (CV12) and Weishu (BL21) are the alarm and transport points of the stomach and can be used to treat diseases related to this organ. Thus, Zhongwan (CV12) and Weishu (BL21) were selected for use in one of the acupuncture treatment groups.

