### Outcome measurements

Patients will be required to complete the Chinese version of the Nepean Dyspepsia Index (NDI), which has been translated according to the validated long version of the Nepean Dyspepsia Index (NDI) [25]. The reliability and validity of this index were tested in the first phase of the ***973 program***. Patients will also be asked to complete the Symptom Index of Dyspepsia and the Mos 36-item Short Form Health Survey (SF-36). The Symptom Index of Dyspepsia focuses on four symptoms, namely postprandial distension, early satiety, epigastric pain and heartburn. Each symptom is then graded as asymptomatic (0 point), mild (1 point), moderate (2 points) or severe (3 points). The SF-36 is a Chinese version of an English test [2] to assess the quality of life.

The main outcome measurements in this trial will include differences in the Nepean Dyspepsia Index (NDI) and the Symptom Index of Dyspepsia, as measured before randomization, 2 weeks and 4 weeks after randomization, and 1 month and 3 months after the completion of treatment. Secondary outcome measures will include differences in the SF-36 before randomization, 4 weeks after randomization, and 1 month and 3 months after completing treatment.

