The theory of TCM and acupuncture strongly suggests that acupoints and non-acupoints differ in their abilities to promote specific physiological effects. Acupuncture is gradually becoming more accepted in countries beyond China, including in Western countries, as a potential treatment for a wide array of diseases. Indeed, this method has been used in clinical practice for many years. In recent years, differences in the "specific" and "non-specific" effects of acupoints have been examined by some Western studies [22,27,28]. According to TCM, there are differences between closely related meridians and other meridians, and there are also differences between specific acupoints (such as five transport points, alarm points, or transport points) and non-specific acupoints. Thus, a specific acupoint for the stomach meridian will be stimulated in group 1, a non-specific acupoint for the stomach meridian will be stimulated in group 2, alarm and transport points will be selected in group 3, and the gallbladder meridian (selected as being representative of other non-specific disease-related meridians, with a similar specific acupoint as that used in group 1) was stimulated in group 4. We have examined all relevant acupuncture literature and have analyzed the frequencies of acupoint during the first phase of our ***973 program***. The results indicate that the most commonly used acupoints are specific acupoints, such as Zhongwan (CV12, an alarm point), Zusanli (ST36, five transport points, in the meridian of the stomach), and Weishu (BL21, a transport point).

Most previous acupuncture trials were performed using semi-standardized acupuncture protocols. In this trial, we will restrict the number of acupoints and standardize the manipulation procedure. These actions have two merits: First, it is better to blind patients from the type of acupuncture they are receiving and second, some confounding factors (such as special rituals of acupuncture) will be excluded from the analysis, thereby making the acupuncture groups more comparable. However, this study design has its limitations; for example, the use of limited acupoints may not be an optimal acupuncture treatment protocol.

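### Two unranked primary outcomes, four visits and three families of arm comparisons are tested at P < 0.05 with no deciding test, so the plan does not hold its 5% error rate

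*Protocol article*

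**What the plan says.** **Outcomes and visits.** The Outcome measurements section states: "The main outcome measurements in this trial will include differences in the Nepean Dyspepsia Index (NDI) and the Symptom Index of Dyspepsia". For both outcomes it lists five assessment times, a baseline and four later visits: "as measured before randomization, 2 weeks and 4 weeks after randomization, and 1 month and 3 months after the completion of treatment". Neither outcome is placed above the other, and none of the four post-baseline visits is named as the deciding one.

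**Hypotheses.** The Statistical analysis section introduces its list with "The two-sided null hypotheses to be tested include". The first item reads "The primary outcomes of the acupoint treatment groups will be equivalent to those of the itopride control group". The second makes the same statement against the non-acupoint group, and the third compares the acupoint groups with each other. The error level is given once: "We will test these hypotheses with a significance level of P < 0.05".

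**Order of steps.** Step 2 compares acupoints with itopride. Of step 3 the section says: "The third step will involve comparing the acupoint treatment group with the non-acupoint control group". Here the group is singular, while the second hypothesis has groups in the plural. Step 4, between acupoint arms, is run only if acupoints prove more effective than non-acupoints. Step 3 does not depend on step 2.

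**Model.** The same section adds repeated measures analysis and mixed models covering baseline to 3 months, without naming the contrast that decides.

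**Gallbladder arm.** The Rationale for selecting acupoints says of this meridian that "it is anatomically close to the stomach meridian and therefore may achieve similar effects". The Discussion describes it as "selected as being representative of other non-specific disease-related meridians".

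**The concern.** The two main conclusions of the trial are that acupuncture works in functional dyspepsia and that points differ. Each can be drawn from any of several outcomes, visits and arms, and the text gives no rule for which result counts. A single 5% level spread over that many openings is no longer 5% for the conclusion.

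The one gate, before step 4, does not repair this. It protects neither step 2 nor step 3, and its trigger is tied to no outcome, visit or arm. A chance finding in step 3 can therefore open the specificity analysis. If step 3 is instead read as one pooled comparison, arms that work less well could keep the gate shut. These are alternative readings of an unclear sentence, and the two harms do not add together.

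The two accounts of the gallbladder arm change no error rate. They do leave equality with the stomach meridian, or a difference from it, open to being read afterwards as what the theory expected.

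**Working it through.** The plan gives no overall error rate to reproduce; the figure to compare with is its 5%.

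**Count of comparisons**
- Acupoint arms against itopride: 4.
- Acupoint arms against non-acupoints: 4.
- Between acupoint arms: 4 × 3 / 2 = 6, only if step 4 opens.
- At most 4 + 4 + 6 = 14 contrasts. With 2 outcomes and 4 visits, 14 × 2 × 4 = 112 tests; with step 4 shut, 8 × 2 × 4 = 64. These are upper limits.

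**Simulation under no true differences.** Six equal arms (1:1:1:1:1:1 allocation), two-sided 5% z-tests, with comparisons that share an arm correlated accordingly. For arms i and j, z = (mean i − mean j) / √2 with each mean in standard-error units. For the pooled reading, z = (mean of the four acupoint arms − control) / √1.25. The correlations between outcomes and between visits are not in the protocol; both are assumed, from 0.8 down to 0.3.

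Chance of at least one false positive in steps 2 and 3, either direction:

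| Reading | Chance |
|---|---|
| 8 contrasts, one outcome, one test each | 27% |
| 8 contrasts, both outcomes, one test each | 38–45% |
| 8 contrasts, both outcomes, four visits tested separately | 66–89% |
| Arms pooled (2 contrasts), both outcomes, one test each | 15–18% |

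Chance of a false result favouring at least one acupoint arm over non-acupoints:

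| Reading | Chance |
|---|---|
| Both outcomes, one test each | 12–14% |
| Both outcomes, four visits tested separately | 23–41% |

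**Step 4, once open.** If the four acupoint arms are truly equal, the six pairs give a false difference with chance 20% for one outcome at one visit, and 54–80% for both outcomes at four visits.

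**Price of control.** The detectable NDI difference at 90% power is (critical value + 1.282) × 22 × √(2/n), with SD 22 from the protocol. The two-sided Dunnett critical value for four arms against one control is about 2.44.
- n = 120: 22 × √(2/120) = 2.84. Unadjusted, (1.96 + 1.282) × 2.84 = 9.2. Dunnett, (2.44 + 1.282) × 2.84 = 10.6.
- n = 102 (120 less 15% withdrawal): 22 × √(2/102) = 3.08. Unadjusted 10.0; Dunnett 11.5.

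These differences are worked back from n and are not protocol figures. The protocol's own difference is 3.0 points, which with its SD and power would need 1131 per group two-sided before withdrawal. That is a separate matter.

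**The case against.** The strongest reply is that the text tests three hypotheses at 0.05 and nowhere orders 112 tests. The mixed model could give one joint test per outcome, and a condensed article commonly leaves multiplicity procedures to an analysis plan.

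Much of this stands. Separate tests at each visit are permitted, not prescribed, so 66–89% is the upper reading and not the expected one. A reader might infer that most trials with no real effect would end in a claim of acupoint efficacy. The document does not support that: the upper figure counts both directions and the itopride contrasts, including results in which acupoints do worse. The error that matches an efficacy claim is 12–14%, or 23–41% with four visits. With arms pooled and one test per outcome, it falls to 4–5%, though the nominal one-sided share is 2.5%.

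The appeal to an analysis plan stands only in part. The article itself fixes two equal primary outcomes, the visits, the hypotheses, the level and the order of steps. A later plan would have to choose among outcomes already declared equal. Every reading computed for steps 2 and 3 together exceeds 5%.

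The gallbladder wording is a tension and no more: one place says what may happen, the other gives the arm's role, and the hypothesis is two-sided.

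**Conclusion.** The concern holds as a should-fix. As written, the plan does not keep the chance of a false positive in the control comparisons at 5%. That chance is about three times nominal on the most lenient reading (15–18%) and 38–45% arm by arm with one test per outcome. The wider figure of 66–89% applies only if visits are tested one by one.

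The 27% figure needs no assumed correlation, because the dependence between arms follows from the equal allocation and shared controls. The ranges rest on assumed correlations of 0.8 to 0.3 and on no true differences anywhere. The wording does not settle whether step 3 is arm by arm or pooled, so the plan has no single error rate until that is stated.

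**What to change.** 1. Make NDI, the outcome used for the sample size, the single primary outcome. Name one deciding contrast from the mixed model at one visit before unblinding, for example week 4, the end of treatment. Make SID and the other visits secondary.
2. State the itopride and non-acupoint comparisons as two separate questions, neither gating the other, each with Dunnett or Holm control across the four arms. This holds 5% for each question, and so at most 5% + 5% = 10% over both; the plan should say so. Making step 3 wait for success in step 2 would be unwise, since the protocol anticipates 15.0 points for acupuncture and 18.0 for itopride.
3. State that step 3 is tested arm by arm. Open step 4 when at least one acupoint arm beats non-acupoints, without requiring both arms of a contrast to pass. Such a requirement would block group 1 versus group 2 if group 2 failed against non-acupoints, which is a pattern that point specificity would predict.
4. In step 4, use Holm or Tukey control over the six pairs, or a short list of planned two-sided contrasts that includes group 3 (alarm and transport points).
5. State the expectation for the gallbladder arm once, reconciling the Rationale for selecting acupoints with the Discussion.

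**Cost.** No added patients or visits. SID loses its primary status, which is a change of substance and should be recorded as an amendment. Dunnett control raises the detectable NDI difference from 9.2 to about 10.6 points at 120 per arm, or from 10.0 to about 11.5 at 102 evaluable per arm.

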### Blinding

As the acupuncturists are responsible for sending randomization information and receiving notices of group assignments, it would not be practical to blind the acupuncturists to treatment allocations and patients' symptoms. Additionally, it is not possible to prevent patients from knowing if they have received acupuncture or itopride treatment. However, it is feasible and ethical to blind patients to the type of acupuncture they receive. In addition, we intend to conceal the group assignments from outcome assessors and our statistician. To assist with the blinding procedure, we named the groups A, B, C, D, E, and F in the medical records and case report forms (CRFs). The specific acupoints (or non-acupoints) will not be mentioned in these forms.

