### Quality control

All acupuncturists are required to undergo special training, including theoretical and practical lessons, before participating in the trial. All researchers and clinicians must understand the purpose and design of this trial, as well as treatment strategies and measures of quality. In addition, acupuncturists will be trained to use the central randomization method, complete the CRFs and electro-CRFs, locate the points and manipulate the needles. Acupuncturists who have completed the required training and have passed an examination will be considered qualified to assist with this trial. Several trained outcome assessors, who are blinded to group assignment, will be responsible for the outcome assessment. Additionally, to maintain accuracy and quality throughout our clinical study, audits will be conducted on CRF completion and compliance with standard operation procedures (SOPs). Finally, quality control and assurance will be presented in written form by trained monitors at every participating hospital once a month. Patient compliance and voluntary withdrawal from the study (including the reason for withdrawal) will be fully documented.

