The analyses of baseline characteristics, as well as the primary, secondary and other outcomes, are based on the intention-to-treat (ITT) principle. Data distribution is expected to be normal owing to the large sample size. However, any skewed distribution data will be transformed prior to analysis. The repeated measures analysis will be used in the assessment of different time points (such as comparing NDI scores before randomization, 2 weeks and 4 weeks after randomization, and 1 month and 3 months after the completion of treatment). Missing values will be addressed using the method of last observation carried forward (LOCF) and multiple-imputation. We will perform sensitivity analysis to determine how these two methods affect the analytic results. General linear mixed models, adjusted for clinical site, will be used to study the effects of treatments on outcomes from baseline to 3 months. Additionally, time-to-event outcomes between groups will be compared using the log-rank test.

Analysis of data will be performed in a blinded manner by a designated statistician at the National Clinical Trial Center of Chinese Medicine (Chengdu GCP Center) in China. Statistical analyses will be performed using SPSS 15.0 statistics software (SPSS Inc, Chicago, Illinois, USA) and SAS 9.0 (SAS Institute Inc., Cary, North Carolina, USA).

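### The ITT basis set for all primary outcomes is not conservative for the intended non-inferiority reading against itopride, so a supporting per-protocol analysis should be added for that comparison

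*Protocol article*

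**What the plan says.** **Analysis set.** Under Statistical analysis, the protocol article states: "The analyses of baseline characteristics, as well as the primary, secondary and other outcomes, are based on the intention-to-treat (ITT) principle". It makes no exception for the itopride comparison and names no per-protocol or other set. Missing values are to be handled by LOCF and multiple imputation. The one sensitivity analysis described compares those two methods.

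**Aim of the itopride comparison.** The same section lists three two-sided null hypotheses. The first is: "The primary outcomes of the acupoint treatment groups will be equivalent to those of the itopride control group". No non-inferiority margin is given. The Discussion then says of the choice of itopride that "we will attempt to maintain a non-inferiority design because acupuncture is associated with no significant side effects".

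**Retention.** The Blinding section concedes that "it is not possible to prevent patients from knowing if they have received acupuncture or itopride treatment". The Discussion draws the consequence: "This factor may cause a high drop-out rate in the itopride group because patients will expect to receive acupuncture treatment when they join the trial". The countermeasure is that "patients in the itopride group will be provided with 10 sessions of free acupuncture after the entire trial has been completed". The sample-size paragraph allows for 15% withdrawal overall and does not split it by arm.

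**Adherence data.** Under Quality control: "Patient compliance and voluntary withdrawal from the study (including the reason for withdrawal) will be fully documented". The article does not link these data to any analysis set.

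**The concern.** ITT is the usual cautious choice for a test of difference, because non-adherence shrinks differences and makes superiority harder to show. In a non-inferiority comparison the same shrinkage works in favour of the claim. Itopride patients who stop or under-use the drug remain in the itopride mean, lower it, and bring it closer to acupuncture. If patients improve over time, LOCF of early scores from those who leave acts in the same direction.

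The article itself expects the retention problem to fall on the active-control arm, which is the unfavourable side for this comparison. There is also no drug-placebo arm among the six groups, so nothing inside the trial would show that itopride had performed below its usual level. At stake is whether a statement that acupuncture is no worse than itopride reflects the treatments or reflects itopride not being taken.

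**Working it through.** **The plan's own figure.** The article gives no error rate for a non-inferiority reading. The nearest figure is the sample size: difference 3.0, SD 22.0, 90% power, 5% significance, 120 per group. The standard two-sided formula gives 2 × (22 × (1.960 + 1.282) / 3)², which rounds up to 1131 per group, so 120 is not reproduced. That is a separate matter. Here 120 per arm is taken as given, and the mismatch matters only for precision.

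**Inputs from the article (Statistical analysis).** Improvement in NDI score of 18.0 with itopride and at least 15.0 with acupuncture (15.0 used here); SD 22.0; 120 per group.

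**Assumptions, not in the article.**
- The margin is 3.0. The article calls this difference minimally significant, not a margin.
- The test is one-sided at 2.5%, for one acupoint group against itopride.
- The true deficit among patients who stay on treatment is 18.0 − 15.0 = 3.0, exactly at the margin.
- Stopping rates by arm and the improvement kept by stoppers are varied below.
- Stopping is unrelated to prognosis, and outcomes are observed.

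**Formulas.**
- SE = 22 × √(2/120) = 2.840.
- ITT mean of an arm = on-treatment improvement × (1 − stop rate) + improvement in stoppers × stop rate.
- ITT deficit = itopride mean − acupuncture mean.
- P(non-inferiority declared) = Φ((3.0 − deficit)/SE − 1.960).

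**Results.**

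| Stop itopride / acupuncture | Improvement in stoppers | ITT deficit | P(declared) |
|---|---|---|---|
| 0% / 0% | – | 18.0 − 15.0 = 3.00 | Φ(−1.960) = 2.5% |
| 15% / 15% | none | 15.30 − 12.75 = 2.55 | Φ(0.158 − 1.960) = 3.6% |
| 15% / 0% | half (9.0) | 16.65 − 15.00 = 1.65 | Φ(0.475 − 1.960) = 6.9% |
| 25% / 0% | half (9.0) | 15.75 − 15.00 = 0.75 | Φ(0.792 − 1.960) = 12.1% |
| 15% / 0% | none | 15.30 − 15.00 = 0.30 | Φ(0.951 − 1.960) = 15.6% |
| 25% / 10% | none | 13.50 − 13.50 = 0.00 | Φ(1.056 − 1.960) = 18.3% |

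Equal stopping does little, so the effect comes mainly from imbalance between the arms. The last row is the most extreme case shown and is not an upper bound.

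**Precision.** The 95% half-width at 120 per arm is 1.96 × 2.840 = 5.6 points, wider than the assumed margin. Even with two truly equal treatments, non-inferiority at 3.0 would be shown only Φ(3/2.840 − 1.960) = 18.3% of the time. Low precision therefore hides part of the bias. At 1131 per arm, 15% stopping itopride only with half the benefit kept would give 31% instead of 6.9%.

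**The case against.** **The article does not say ITT alone.** A reader might infer that the plan restricts every comparison to the ITT set. The text bases the outcomes on ITT and names nothing else. A supporting per-protocol set is something an analysis plan, not shown here, could add. This stands, so the point is not that a set is missing. It is that the stated rule covers the itopride comparison without exception, although the article's own expectations make the rule favourable to the claim there.

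**Non-inferiority is not defined in the analysis section.** The hypotheses are two-sided with no margin, and non-inferiority appears only in the Discussion as something to be attempted. This also stands. The contradiction must be resolved first, and 3.0 is only an assumed margin. It does not remove the concern, because a non-significant result or a confidence interval read as non-inferiority is shifted the same way.

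**Drop-out is not the same as staying in follow-up off the drug.** A reader might infer that the article predicts itopride patients who stop the drug but still give outcomes. It speaks of drop-out and withdrawal, which are naturally read as leaving the trial. That part is a missing-data question, and LOCF and multiple imputation are planned for it. LOCF can push in the same direction, and the comparison of the two methods does not address under-use among patients who stay. The free sessions are meant to prevent drop-out. They give a reason to remain in the trial but not to take the drug, so the net effect on adherence is unknown.

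**The figures depend on assumptions.** The 18.0 is a change after treatment and may include improvement not due to the drug, so removing all of it from stoppers is extreme. The declared non-inferiority is false only if the on-treatment difference is the target. For the effect of assignment, the difference in those scenarios lies inside 3.0. Both remarks are fair.

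**Conclusion.** The point holds in a limited form, as a cheap improvement. For the itopride comparison, and for no other, ITT is not conservative if the result is read as non-inferiority, and the article expects the imbalance that would make this matter. In the illustration, the chance of declaring non-inferiority at an on-treatment deficit equal to the margin rises from 2.5% to 3.6% with equal 15% stopping and no benefit in stoppers. It rises to 6.9% with 15% stopping itopride only and half the benefit kept, and to about 18% with 25% against 10% stopping and no benefit.

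These rates rest on an assumed margin and on assumed stopping rates and residual benefit. They are not estimates of this trial's error rate. A reader might go further and conclude that a false non-inferiority claim is likely. The documents do not support that, because they give no stopping rates by arm and precision at 120 per arm is low. Nor is ITT wrong for the comparisons with non-acupoints or between acupoint groups, where differences are tested.

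**What to change.** First reconcile the Discussion's non-inferiority intention with the two-sided null in hypothesis 1, and state a margin if non-inferiority is to be claimed. Then, for hypothesis 1 only:

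- add a per-protocol analysis, with its adherence and deviation criteria written down before unblinding and drawn from the compliance and withdrawal data already recorded;
- report it beside the ITT analysis;
- claim non-inferiority only if the confidence limits from both analyses support it.

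Keep ITT for hypotheses 2 and 3.

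The cost is one paragraph and one extra analysis run, with no new data collection and no change in sample size on this account. At the article's 15% withdrawal, about 120 × 0.85 = 102 per group would remain, and fewer if some completers are also non-adherent. The downside is that the claim becomes harder to reach. The per-protocol set is smaller, is not fully protected by randomization and can be biased in either direction, so it supplements ITT and does not replace it.
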